## Outcome assessments

3

### Primary outcome measures

3.1

As the oral and genital ulceration, skin lesions (erythema nodosum) are most common complaints in BD patients. We select a mucocutaneous activity index (MAI) in BD created by Mumcu et al.^[14]^ In this MAI:Presence of the lesion was coded as 1 for actives and 0 for inactives (0 vs 1 point)Pain was evaluated by 100 mm-visual analogue scale (VAS; 0: no pain–100: severe pain) by patients. Then, the VAS score was categorized to calculate the score as follows: ≤10: 0; 11–20: 1; 21–40: 2; 41–60: 3; 61–80: 4; 81 and over: 5 points.Functional status was evaluated by a 5-point Likert-type scale: none of the time (0 points), little of the time: 1 point, some of the time: 2 points, most of the time: 3 points and all of the time: 4 points. Mean score was used in the index (Table 2).

**Table 2 T2:**
[figure not shown]
Mucocutaneous activity index and its subscales in BD.

Based on the follow-up of the MAI and other-related symptoms in BD, the remission ratio after treatment will be accessed. The remission degree will be divided into 4 levels:Cured: All of the BD manifestations disappeared, rare relapse (less than 2 times a year) after stop treatment for more than 1 year.Complete remission: Most of the BD manifestations disappeared (MAI reduce ≥3 points), occasionally relapse (less than 4 times a year), but could easily manage by the treatment.Partial remission: Some of the BD manifestations disappeared; the frequency of relapse is less than before treatment.No effect: BD manifestations not respond to the treatment, relapse during the treatment.

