### Objective

2.1

The primary objective of this study is to ascertain the potential curative or improvement effects and safety of GDPSF for BD patients with mucocutaneous involvement only. The secondary objective is to determine whether combination application of GDPSF and thalidomide could possibly reduce the side effects caused by thalidomide and increase effectiveness for BD management.

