### Study design

2.2

This is a single center, double-blinded, randomized, and controlled, parallel-group study. Figure 1 depicts a flow chart of the study. Patients enrolled in this study will randomly be assigned into 3 different groups with respective treatment. Clinical manifestations, blood inflammatory index including erythrocyte sedimentation rate (ESR), C-reactive protein (CRP), and some of the blood biochemical tests will be checked before treatments started (baseline) and will be reexamined on week 4, 8, 12, 18, 20, and 24 during 6 months of treatment to assess the effectiveness and safety. Try to follow up every participant in another 12 months to compare satisfactory rate, complete and partial remission rate, and ineffective rate in different treatment groups.

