### Groups and interventions

2.6

Included patients will be randomly allocated into 3 groups: GDPSF group, thalidomide group, and integrative group. GDPSF group will receive GDPSF and placebo pills of thalidomide size, color, and shape made from cheese. Thalidomide group will take 100 mg thalidomide pill every night and placebo water of GDPSF color and amount. Integrative group will receive both GDPSF and thalidomide, which dosage could be flexible, range from 25 to 100 mg as long as the symptoms could be controlled during the treatment period. All of the patients in these 3 groups will take their medications for 6 months duration.

GDPSF composed of 7 herbs, including 12 g *Glycyrrhiza uralensis* (GanCao), 9 g *Scutellaria baicalensis* (HuangQin), 12 g *Pinellia ternate* (BanXia), 3 g *Coptis chinensis* (HuangLian), 9 g *Zingiber officinale* (GanJiang), 9 g *P ginseng* (RenSheng), and 12 piece of Jujube (HongZhao). The components of formula will be decocted in Herbs Dispensary of our hospital by herbs tisanes machine, into 3 sealed bags of liquid, 200 mL for each bag. Patients can save the herbal decoction in refrigerator and warm it in microwave oven before taken.

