### Statistical analysis

4.2

This is an 18 months clinical trial, in which participants will receive treatment for 6 months and accept a 12 months follow-up. During their treatment, participants will visit investigators every 4 weeks 5 times in all. Their clinical manifestations (MAI), blood tests, thalidomide dosage in thalidomide, and integrative groups will be assessed. Participants will receive 2 times of follow-up for 12 months after treatment, their remission levels, quality of life, and satisfactory levels will be assessed. Figure 3 summarizes the study schedule of enrollment, interventions, and assessments according to the SPIRIT 2013 statement. The data of assessments on each intervention group before and after treatments will be collected and analyzed through historical control, while between groups through intergroup control method.

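### The top remission grade, Cured, needs more than 1 year off treatment, but follow-up stops 12 months after treatment, so a completer cannot reach it on the stated schedule

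*Protocol article*

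**What the plan says.** The remission grading is set out in section 3.1 (Primary outcome measures), after Table 2: "The remission degree will be divided into 4 levels". From best to worst these are Cured, Complete remission, Partial remission and No effect. Cured requires that every manifestation has gone and "rare relapse (less than 2 times a year) after stop treatment for more than 1 year". Complete remission requires most manifestations to have gone (a fall of at least 3 points on the mucocutaneous activity index) and allows fewer than 4 relapses a year.

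The durations are stated in three places and agree with each other:

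- Section 2.6: "All of the patients in these 3 groups will take their medications for 6 months duration".
- Section 4.2: "This is an 18 months clinical trial, in which participants will receive treatment for 6 months and accept a 12 months follow-up". The same section adds "Participants will receive 2 times of follow-up for 12 months after treatment", and says remission levels are assessed at those contacts.
- Section 2.2: "Try to follow up every participant in another 12 months to compare satisfactory rate, complete and partial remission rate, and ineffective rate".

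The primary objective in section 2.1 is to "ascertain the potential curative or improvement effects and safety of GDPSF" in patients with mucocutaneous disease only. The list of rates in section 2.2 contains complete remission, partial remission and ineffective. It contains no cured rate.

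**The concern.** The time condition for the top grade is a strict inequality at one year. The planned observation off treatment ends at one year. No contact beyond that point is described, so a patient treated and followed exactly as planned is never observed for long enough to qualify.

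Two things are at stake. First, the scale loses its upper distinction. A completer with no manifestations and no relapse over 12 months falls into the same grade as one with 3 relapses a year, although the plan meant to separate them and its primary objective speaks of curative effects. Second, if the grade is used anyway, someone must decide later how to read the one-year rule and where a Cured patient counts in the section 2.2 comparison. Those would be post hoc choices on a primary outcome.

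This is not a detail that can be left to an analysis plan. The grade definition and both durations are stated in the article and conflict, and an analysis plan cannot create observation time that the design lacks.

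**Working it through.** **Inputs**

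- Off-treatment time needed for Cured: more than 12 months (section 3.1).
- Treatment: 6 months in all three groups (sections 2.6 and 4.2).
- Follow-up: 12 months after treatment, two contacts (sections 2.2 and 4.2).
- Trial length: 18 months (section 4.2).
- Last listed assessment in the treatment period: week 24 (section 2.2).

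**Step 1. Reproduce the plan's own figure.** 6 + 12 = 18 months, as stated.

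**Step 2. Completer, in months.** Longest off-treatment observation = trial length - treatment length = 18 - 6 = 12. The condition is > 12, so it is not met. Had the rule been at least 12 months, a completer could just meet it at the final contact.

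**Step 3. Completer, in days.** Take a month as 365.25 / 12 days.

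- Treatment ends at week 24 and the last contact is at 18 calendar months: 24 × 7 = 168 days on treatment, and 18 × 365.25 / 12 = 547.9 days to the last contact. Off-treatment time is 547.9 - 168 = 379.9 days, about 15 days over a year (379.9 - 365.25 = 14.6).
- The 12 months are counted from the end of treatment: 12 × 365.25 / 12 = 365.25 days, with no excess.

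So the grade is either unreachable or cleared by roughly two weeks, depending on a convention that the text does not fix.

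**Step 4. First follow-up contact.** The text does not date the two contacts. If the first falls near month 12 (an assumption), a completer has been off treatment for about 12 - 6 = 6 months. Cured could not be graded there under either convention in step 3.

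**Step 5. Patients who stop early.** For a stop at month m, the result depends on where the 12 months start:

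| Stop at month m | Observation ends at month 18: 18 - m | 12 months from own stop |
|---|---|---|
| 2 | 16 (more than 12) | 12 (not more than 12) |
| 4 | 14 (more than 12) | 12 (not more than 12) |
| 5 | 13 (more than 12) | 12 (not more than 12) |
| 6 (completer) | 12 (not more than 12) | 12 (not more than 12) |

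The completer row is the same under both anchors.

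**Step 6. What is lost from the scale.** Cured allows 0 or 1 relapse a year, and Complete remission allows up to 3. If Cured is empty, patients with 0 to 1 and with 2 to 3 relapses a year can share one grade, and 4 levels become 3.

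**The case against.** The best defence is that this is a boundary mismatch of no great consequence. A slightly late last visit, the week-24 convention, or reading the rule as at least a year would let completers qualify. Figure 3 could not be read here and may give contact dates that help. The rule applies equally to all three groups, so an empty grade does not by itself favour any of them. The mucocutaneous activity index, also under the primary outcome, is untouched, and the study is described as a pilot.

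Much of this stands. It rules out saying that no completer could ever qualify under any reading, and it rules out a claim of built-in bias between groups. It does not rescue the text, because a top grade decided by about 15 days of visit timing is still badly fixed. Another reading makes matters worse: if relapses are to be counted only after the first year off treatment, still longer follow-up is needed.

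A reader might go further than the documents allow in three ways:

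- **That only early stoppers or treatment failures could be Cured.** This holds for early stoppers only if observation ends at month 18 for everyone. Section 4.2 speaks of 12 months after treatment, and counted from a patient's own stop nobody qualifies. Treatment failures cannot qualify at all, because every manifestation must have gone. Patients stopped for a serious adverse event are referred to other treatment (section 4), so they may not be off treatment.
- **That up to 30 patients (20% of 150) could qualify.** The 20% in section 4.1.1 is an anticipated dropout rate. Nothing says that these patients stop study medication early and remain under observation to month 18.
- **That the section 2.2 comparison penalises the best group.** The penalty arises only if the grade can be reached and Cured patients are left out of the complete remission rate. The text states neither. What can be said is that section 2.2 does not show where a Cured patient counts.

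**Conclusion.** The point holds as a contradiction between the definition of the top grade and the length of follow-up. On the stated schedule a completer has at most 12 months off treatment against a requirement of more than 12. The grade is then empty, or is reached by about 15 days under one calendar convention, and the four-level scale in effect has three levels. The omission of a cured rate from section 2.2 adds an ambiguity about counting; it is not a demonstrated distortion.

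The conclusion rests on the durations in the text and on there being no planned contact later than 12 months after treatment. It does not depend on sample size, dropout or effect size. Confidence is high for the mismatch itself. The documents do not support any statement about which patients would benefit from it, or how many.

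**What to change.** Reconcile the time condition for Cured in section 3.1 with the follow-up in sections 2.2 and 4.2 before any patient is graded at the final contact. One workable wording:

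- **Top grade:** all manifestations absent at the final follow-up contact, and fewer than 2 relapses during the 12-month post-treatment follow-up. Grade it at that contact only.
- **Anchor:** state one date from which the 12 months run, and apply it to all patients, including those who stop early.
- **Other treatment:** do not count patients who moved to other treatment for Behcet disease as off treatment.
- **Section 2.2:** compare complete remission or better, so that any patient in the top grade stays in the numerator.

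The cost is a few sentences in sections 2.2 and 3.1, with no extra visits or patients. The downside is that the grade claims slightly less than the present wording, a relapse record over 12 months instead of more than a year. If the sponsor wishes to keep more than 1 year, follow-up has to run past month 18. Whether the word curative stays in the objective is a matter of preference and is not part of this point.

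### The four remission levels of the primary outcome do not give each patient exactly one grade, whichever way the comma in No effect is read

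*Protocol article*

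**What the plan says.** Section 3.1 of the Protocol article (Primary outcome measures, text below Table 2) states that "The remission degree will be divided into 4 levels". The three lower levels matter here:

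- **Complete remission:** most manifestations gone, with an MAI reduction of at least 3 points, and "occasionally relapse (less than 4 times a year), but could easily manage by the treatment".
- **Partial remission:** "Some of the BD manifestations disappeared; the frequency of relapse is less than before treatment".
- **No effect:** "BD manifestations not respond to the treatment, relapse during the treatment".

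The top level, Cured, requires all manifestations gone and "rare relapse (less than 2 times a year) after stop treatment for more than 1 year".

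The text shown gives no rule for a patient who fits two levels or none. It also does not fix the year over which relapses are counted. Section 4.2 says that "participants will receive treatment for 6 months and accept a 12 months follow-up". Section 2.2 compares complete and partial remission rates and the ineffective rate between groups, and section 4.2 assigns count data to a chi-square test.

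**The concern.** A division into levels has to place every patient in one level and only one. The chi-square comparison needs the same thing: each patient counted once, in one cell.

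The difficulty lies in the lowest level. It consists of two clauses separated by a comma, with nothing to say whether either one suffices or both are required. The second clause concerns relapse on treatment and carries no number, while Complete remission expressly tolerates up to three relapses a year. Depending on the grader's reading, a relapse on treatment is either compatible with the second-best level or also satisfies the worst one. Partial remission adds a further loose end, because its wording sets no upper limit on improvement.

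The complete remission, partial remission and ineffective rates are what the trial will report for this outcome. If they depend on an unstated reading, two careful graders can produce different rates from the same patients.

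**Working it through.** The plan states no figure on this point, so there is nothing to reproduce. The check is a cross-classification, followed by one illustration of size.

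**Inputs from section 3.1.** CR (Complete remission): most manifestations gone (MAI down at least 3) and fewer than 4 relapses a year, that is 0 to 3, taken here as manageable. PR (Partial remission): at least some manifestations gone and relapse frequency lower than before. NE (No effect): non-response and/or relapse on treatment. Cured is left out because it plays no part in the conflict. The table uses the same count for relapses on treatment and in the year, except where noted.

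| Response | Relapses | Frequency lower than before? | Comma = *or* | Comma = *and* |
|---|---|---|---|---|
| None | 0 | either | NE | no grade |
| None | 1 or more | either | NE | NE |
| Some | 0 on treatment | yes | PR | PR |
| Some | 0 on treatment | no | no grade | no grade |
| Some | 1 or more | yes | PR and NE | PR |
| Some | 1 or more | no | NE | no grade |
| Most | 0 | yes | CR and PR | CR and PR |
| Most | 0 | no | CR | CR |
| Most | 1 to 3 | yes | CR, PR and NE | CR and PR |
| Most | 1 to 3 | no | CR and NE | CR |
| Most | 4 or more | yes | PR and NE | PR |
| Most | 4 or more | no | NE | no grade |

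Of the 12 patterns, *or* gives exactly one grade in 6, more than one in 5 and none in 1. *And* gives exactly one in 6, more than one in 2 and none in 4. These are counts of patterns, not of patients.

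The CR and PR overlap is present under both readings. The CR and NE overlap exists only under *or*. The non-responder without a relapse lacks a grade only under *and*.

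**Illustration of size, *or* reading only.** The document gives no relapse rate, so rates of 1, 2 and 3 a year are assumed. Relapses are taken as Poisson with the same rate on and off treatment, and the counting year is assumed to contain the 6 treatment months. The chance of at least one relapse on treatment is 1 − exp(−rate/2):

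- rate 1: 1 − exp(−0.5) = 39%
- rate 2: 1 − exp(−1) = 63%
- rate 3: 1 − exp(−1.5) = 78%

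Complete remission also requires 3 or fewer relapses in the year. With S(x) = 1 + x + x²/2 + x³/6, the share with at least one relapse on treatment, given 3 or fewer in the year, is 1 − S(rate/2)/S(rate):

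- rate 1: 1 − 1.646/2.667 = 38%
- rate 2: 1 − 2.667/6.333 = 58%
- rate 3: 1 − 4.188/13 = 68%

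So, among patients who otherwise qualify for Complete remission, 38% to 68% would also meet No effect. If exactly 1, 2 or 3 relapses are instead spread evenly over the 12 months, the chance that at least one falls in the treatment half is 1 − 0.5^k, that is 50%, 75% or 87.5%.

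**The case against.** The strongest reply is that the conflict between the worst and second-best levels depends on reading the comma as *or*. In Cured and Complete remission the comma joins conditions that must all hold. Read the same way, No effect is non-response together with relapse, and a patient with most lesions gone cannot be graded there. That is at least as natural a reading, and it stands. A reader might infer that No effect takes in any relapse on treatment, but neither *any* nor *or* appears in the definition. The *and* reading does not rescue the scale, however, because it leaves the non-responder without a relapse ungraded.

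It can also be said that in a recurrent disease most non-responders will have new episodes on treatment, so the gap under *and* may be small. That is fair. The document gives no basis for sizing the gap, nor for saying that a patient with persistent lesions cannot relapse.

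A reader might infer that an improved patient with 4 or more relapses a year and an unchanged frequency has no grade under either reading. That goes too far. Under *or*, a single relapse on treatment places this patient in No effect, and at 4 relapses a year the chance of at least one in 6 months is 1 − exp(−2) = 86%. The gap belongs to *and*, or to patients whose relapses all fall after treatment.

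The illustration can be pushed further. Suppose 20 of 40 evaluable patients are in complete remission at 2 relapses a year. Then 20 × 0.58 = 11.6 also meet No effect, and the rate could be 50% or (20 − 11.6)/40 = 21%. The arithmetic is right, but the inputs are assumed and No effect must override Complete remission in every such patient. Section 4.2 assesses remission levels in the follow-up after treatment. If relapses are counted over that year alone, these shares do not apply.

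A reader might also infer that knowledge of the group will steer grading. Section 2.5 states that neither patients nor doctors know the allocation, and the point does not need that argument.

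Finally, grading instructions are often left to a fuller document, and the levels are already listed from best to worst. But these definitions are given in full under the primary outcome, and as worded they do not divide patients. The trial calls itself a pilot and also specifies the MAI score, which is unaffected. That limits the damage but does not repair the levels.

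**Conclusion.** The point holds in this form: the four levels are not mutually exclusive and exhaustive under either reading of No effect. *Or* creates an overlap with Complete remission and with Partial remission. *And* removes those overlaps but leaves some patients, including non-responders without a relapse, ungraded. The overlap of Complete with Partial remission survives both readings, although an order of grading resolves it at once. This conclusion rests on the wording alone.

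The size is uncertain. The 38% to 68% range holds only under *or*, with assumed Poisson rates of 1 to 3 relapses a year, equal on and off treatment, and a counting year that contains the treatment period. No size can be given for the gap under *and*. The documents do not support saying that No effect certainly captures every relapse on treatment, or that an arm's complete remission rate will move by a particular amount. Because the levels feed the rates to be compared between groups, the wording should be settled before grading starts.

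**What to change.** In section 3.1, state that the levels are applied in sequence from best to worst and that each patient receives the first one met. Make No effect the residual level for everyone who meets none of the higher three, expressly including non-response without relapse and worsening. State the period over which relapses are counted, and whether it includes the 6 treatment months.

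The clause on relapse during treatment and the relapse limit in Complete remission must be reconciled. How much weight a relapse on treatment should carry is for the investigators to decide and write down before grading starts.

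The cost is a few words in section 3.1 and on the grading form. No new data are needed.

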### Secondary outcome measures

3.2

Blood inflammatory index including ESR, CRP, and some of the blood biochemical tests such as IgA, IgD, IgE, and IgM, and gamma-glutamyl transpeptidase will be checked before treatments started (baseline) and will be reexamined on week 4, 8, 12, 18, 20, and 24 during 6 months of treatment to assess the effectiveness.

Satisfactory ratio on effectiveness: Every half a year, the controlling on the BD symptoms will be evaluated by patients’ own intuition. VAS for pain is mimicked by the satisfaction scale (Fig. 2).

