**Figure 3 F3:**
[figure not shown]
Schedule of enrollment, interventions, and assessments (using the SPIRIT 2013 statement). AE = adverse event, BD-QoL = quality of life for Behcet disease, CRP = C-reactive protein, ESR = erythrocyte sedimentation rate, GDPSF = Glycyrrhizae Decoction for Purging Stomach-Fire, GGT = gamma-glutamyl transpeptidase, Ig = immunoglobulin, MAI = mucocutaneous activity index.

IBM SPSS 21 Statistics will be applied for the analysis. Measurement data that followed normal distribution will be recorded as mean ± SD and analyzed by ANOVA or *t* test, otherwise, Kruskal–Wallis will be applied. Count data will be analyzed by χ^2^ test. The statistical significance level was set at *P* < .05 for all the tests.

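### Patient satisfaction is collected on a graded, VAS-type scale but named and compared between groups as a rate; comparing the score itself would keep information that any cut into satisfied or not would lose

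*Protocol article*

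**What the plan says.** Three places in the protocol article bear on how satisfaction is measured and compared.

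- **Section 3.2, Secondary outcome measures.** The outcome is introduced as "Satisfactory ratio on effectiveness". Patients rate it every half year by their own judgement, and "VAS for pain is mimicked by the satisfaction scale", with a pointer to Figure 2.
- **Section 2.2, Study design.** The 12-month follow-up is meant "to compare satisfactory rate, complete and partial remission rate, and ineffective rate in different treatment groups".
- **Section 4.2, Statistical analysis.** At the follow-up visits, "their remission levels, quality of life, and satisfactory levels will be assessed". Measurement data go to ANOVA or a t test if normal and to Kruskal–Wallis otherwise. For the rest, "Count data will be analyzed by χ^2^ test". Satisfaction is not assigned to either class.

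The text gives no threshold for calling a patient satisfied. Only the caption of Figure 2 can be read.

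**The concern.** A rate of satisfied patients needs a cut somewhere on the scale. Once the score is cut, two patients at opposite ends of the satisfied range count the same, and so do two at opposite ends of the unsatisfied range. The trial would then test a coarser quantity than the one it holds. The article gives no reason for preferring the coarser one.

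The wording also points two ways: ratio and rate in sections 3.2 and 2.2, levels in section 4.2. Because section 4.2 has tests for both kinds of data, the choice between score and percentage could be made after the results are seen. Section 4.1.1 says the study is to assess the feasibility of a larger trial. For that purpose a mean difference and its SD are useful, and a rate alone does not supply them.

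**Working it through.** **Inputs from the article.** 150 patients, 50 per group, 20% dropout (section 4.1.1); 1:1:1 allocation (section 2.5); significance level 0.05 (section 4.2). Evaluable per group: 50 × (1 − 0.20) = 40. The reverse step, 40 / 0.80 = 50 and 3 × 50 = 150, agrees with the stated total. The article states no effect size, SD, expected satisfaction rate or power, so there is no planned power figure to reproduce.

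**Assumptions not in the article.** Two-sided test, one pairwise comparison, normal scores with equal SD, a true difference of d SD, and a comparator share satisfied p1 of 50%, 70% or 80%.

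**Uncut score.** Two-sample t test with 78 degrees of freedom and noncentrality d × √(40/2). For d = 0.64 this is 0.64 × 4.472 = 2.862, which gives 81% power.

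**Rate.** The same shift moves the satisfied share to p2 = Φ(Φ⁻¹(p1) + d). For d = 0.64 and p1 = 70%, p2 = Φ(0.524 + 0.64) = 87.8%. Summing exact binomial probabilities over all outcomes that the uncorrected chi-square test rejects gives 51% power.

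| d (SD) | t test | Chi-square, p1 = 50% / 70% / 80% | Loss in points |
|---|---|---|---|
| 0.4 | 42% | 30 / 25 / 22% | 12 / 17 / 21 |
| 0.5 | 60% | 43 / 35 / 30% | 17 / 25 / 30 |
| 0.64 | 81% | 61 / 51 / 43% | 20 / 30 / 38 |
| 0.8 | 94% | 78 / 67 / 57% | 16 / 27 / 37 |

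Losses are taken before rounding. Over this grid they run from 12 to 38 points.

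**Outside the grid.** At d = 0.2 the loss is about 2 to 5 points for the same three shares. At d = 1.2 with p1 = 50% it is about 2 points, because both tests are then close to certain to detect the difference. With 90% of comparators satisfied it grows: 53 points at d = 0.64 (81% against 28%) and 59 at d = 0.8 (94% against 35%).

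**Does it depend on the t test?** Less is lost against a rank test, but the direction is the same. In simulation, a Wilcoxon test on a rounded 0–10 scale had 39–40% power at d = 0.4 against 31% for the 50% cut (8 to 9 points), and 92% at d = 0.8 against 57% for the 80% cut (35 points). With skewed 0–100 scores, a Mann–Whitney test gained about 9 to 41 points, depending on the cut. With all three groups compared and one shifted by 0.5 SD, ANOVA had about 62% power against 42%, 33% and 26% for chi-square at the three shares.

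**The case against.** The strongest reply is that the article never says the scale is cut. It prints no threshold, does not assign satisfaction to the chi-square test, and in section 4.2 uses a word that suits a graded measure. Its use of ratio is also loose: section 3.1 announces a remission ratio and then divides remission into four levels. Figure 2 might show categories, and the pain VAS it imitates is itself grouped into six ordered bands in section 3.1. A condensed article may leave the exact test for a secondary outcome to fuller documents.

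Much of this stands. A reader might infer that the trial will certainly dichotomise the score, and the text does not settle that. What remains is that section 2.2 states a comparison of a rate between groups and section 3.2 names the outcome to match. That is stated wording, not an omission. If the scale turns out to have ordered categories, collapsing them to two would still discard information, though by a different amount.

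A reader might also take the section 4.1.1 remark on effective rates generally above 70% as a sign that most patients would fall on one side of the cut. It is not: that figure is a reported treatment response, and nothing links it to patient satisfaction.

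**Conclusion.** The point holds as a minor one. Sections 2.2 and 3.2 name a rate for an outcome measured on a graded scale, section 4.2 uses a different word, and the visible text has no threshold. If the score is reduced to satisfied or not, pairwise power falls by roughly 12 to 38 points against a t test. That range rests on 40 evaluable per group, normal scores, a two-sided 5% test, a difference of 0.4 to 0.8 SD, and 50% to 80% of comparators satisfied.

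It should not be quoted as an unconditional cost of the plan. The effect size, the distribution and the cut are assumed, and the loss ranges from about 2 points to more than 50 as they vary. Nor does the trial lose planned power: satisfaction is a secondary outcome in a self-described pilot, and no power is stated for any outcome. It would also go too far to say that a real difference would probably be missed because of the cut. With 50% of comparators satisfied, chi-square still has 78% power at 0.8 SD, while at 0.4 SD the t test itself has only 42%.

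**What to change.** In sections 2.2 and 3.2, name the satisfaction score as the quantity compared between groups. Analyse it with the measurement-data methods already in section 4.2: ANOVA or t test, or the rank test if the scores are not normal or the scale is ordinal. Report the group difference with a 95% confidence interval. Keep the percentage satisfied as a descriptive figure, with its threshold stated in advance, and align the wording of section 4.2 with this.

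The change needs no new data, visits or patients. Its one small cost is that a difference in scores is less immediate to a clinical reader than a percentage, which is why the percentage is worth keeping alongside.
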